### Sampling method

A two-stage cluster sampling method will be used to ensure adequate sample representation. Khafr County comprises nine comprehensive health centers, including three urban and six rural centers. Additionally, the rural centers will be affiliated with 27 health posts, each responsible for providing services to local families. In the first stage, each urban and rural comprehensive health center will be considered an independent cluster. Three centers (one urban and two rural) will be randomly selected. In the second stage, sampling will be conducted from the population covered by the selected centers. In each rural center, two affiliated health posts will be randomly selected. Then, eligible participants will be randomly chosen from the registries of these health posts and the selected urban center. To maintain equal representation, 50% of participants will be selected from urban areas and 50% from rural areas.

After enrollment, participants will be assigned to one of three groups, walking, meditation, or control, using block randomization. Each block will consist of 6 individuals, with a total of 20 blocks stratified by setting: 10 urban and 10 rural. Allocation concealment will be ensured using sealed envelopes, and responsibilities will be separated so that the person enrolling participants will be different from the one assigning them to groups. Participants will be placed in blocks based on registration order. Each block’s group codes will be enclosed in a sealed envelope. Upon registration of each set of six participants, the envelope will be opened, and codes will be written on separate cards. The randomization coordinator will then be contacted to determine each participant’s group based on the assigned code. This process will be repeated for all participants. A third party using the 2022 version of the Sealed Envelope online tool, independent of both the enrolling staff and the intervention investigator, will perform randomization. To prevent information exchange between groups, the walking and meditation sessions will be scheduled at different times and supervised directly by the researcher.

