**Fig. 1 Fig1:**
[figure not shown]
Study design algorithm: eligibility criteria, random allocation, and follow-up process

Given the active nature of the sessions, participants and those leading the groups will know their assignment. Outcome scores come directly from participant questionnaires, so those results are also unblinded. For the analysis phase, the statistician will work without knowing group labels until the final results are prepared.

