### Requirement

To recruit volunteers, a public and targeted call for participation will be disseminated throughout the nine urban and rural health service centers. This call will aim to inform potential participants about the study and the initial inclusion criteria, providing them with general information to facilitate informed decision-making regarding their participation, based on an understanding of the research objectives and involvement requirements. The call for participation will include details regarding the study title and purpose, general inclusion criteria, duration and format of participation, benefits and incentives for participating, and contact information for registration or further inquiries. This call will be disseminated through various informational methods, including the placement of posters, the organization of introductory meetings, and the distribution of informational messages from the urban and rural comprehensive health service centers.

Upon receiving expressions of interest in participating in the study, volunteers will be screened according to the inclusion criteria by initial interview to assess health history, balance test (Additional File 1), and a Mini-Cog test. Volunteers whose scores on these assessments fall within acceptable ranges will proceed to the next stage of the study. Following screening, comprehensive research information will be provided to eligible participants. This information will include detailed explanations of the study objectives, research methodology, participant commitments, the benefits of study participation, potential risks and limitations, and the right to withdraw from the study at any stage without any consequences. To ensure complete understanding among volunteers, all questions will be addressed.

The principal investigator obtained written informed consent from each participant in person. Following this, the same researcher conducted a face-to-face interview to collect baseline data, which included completing the cognitive empowerment and mental vitality questionnaires. This process will continue until the required sample size is achieved. In this way, all participants will enter the intervention simultaneously, since the study will be a group intervention.

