## Trial status

This protocol is version 1.0, dated June 27, 2025. Recruitment has not yet started. The anticipated start date for participant recruitment is 1 August 2025. The approximate date for completion of recruitment is expected to be 1 March 2026.

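### Arms are allocated block by block during recruitment although all women start together, which leaves an avoidable gap between randomisation and session 1

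*Protocol article*

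**What the plan says.** **Allocation.** The Sampling method section fills blocks in order of entry: "Participants will be placed in blocks based on registration order". The structure is "Each block will consist of 6 individuals, with a total of 20 blocks stratified by setting: 10 urban and 10 rural". The trigger for allocation is a full set of six: "Upon registration of each set of six participants, the envelope will be opened, and codes will be written on separate cards". The next sentence begins "The randomization coordinator will then be contacted to determine each participant" and goes on to the group. Nothing in the article holds the envelopes back until recruitment has closed.

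**Start.** The Requirement section continues consent and baseline interviews until the target number is reached, and concludes: "In this way, all participants will enter the intervention simultaneously, since the study will be a group intervention".

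**Timeline.** Trial status gives both ends of recruitment: "The anticipated start date for participant recruitment is 1 August 2025" and "The approximate date for completion of recruitment is expected to be 1 March 2026". Table 2 (stage 2) gives recruitment and selection 2 weeks.

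**Blinding and analysis set.** The paragraph under Fig. 1 in Study design says "participants and those leading the groups will know their assignment". Data collection and Statistical methods apply intention to treat to everyone initially randomised.

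**The concern.** Rolling allocation is needed when each participant starts on entry. Here nobody starts until everyone is enrolled, so fixing arms early gains nothing and opens a period in which women are randomised but untreated.

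Whatever happens in that period counts as post-randomisation. A woman who withdraws remains in the intention-to-treat set. If no outcome is obtained from her, her data must be imputed. In an open-label trial, withdrawal may depend on the arm: some women assigned to control may lose interest, and some assigned to sessions may decide that the commitment is too large. Behaviour may shift too. The restriction on joining similar group programmes (Study population and setting) covers only the 8-week intervention phase, so it does not protect the wait. Had the same withdrawals come before randomisation, they could not bias the comparison and the women could be replaced.

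This is a separate matter from when eligibility and baseline are measured. Repeating both just before session 1 would not undo an allocation already made.

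**Working it through.** **1. The plan's own sample size.** From the Sample size section: 58 × 1.6 × 1.20 = 111.36, hence 111 (37 per arm). The attrition allowance is 20%, and 20% of 111 is about 22 women. Statistical methods expects up to 14% missing data: 0.14 × 111 = 15.5 women.

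**2. Length of recruitment.** 1 August 2025 to 1 March 2026 is 212 days, and 212 / 30.44 = 7.0 months. Table 2 gives 14 days.

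**3. Wait from allocation to close of recruitment.** Assumption: women register at a uniform rate and both strata fill in parallel. The first block in each stratum is then full after about 12 of 111 registrations. The wait for the i-th pair of blocks is T × (1 − 12i/111), floored at zero. If strata are ignored, 6 replaces 12.

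| | Trial status, T = 212 days | Table 2, T = 14 days |
|---|---|---|
| First blocks, by stratum | 212 × (1 − 12/111) = 189 days (6.2 months) | 12.5 days |
| First block, strata ignored | 212 × (1 − 6/111) = 201 days (6.6 months) | 13.2 days |
| Mean over blocks | 88 to 98 days (about 3 months) | about 6 days |

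Seven months is therefore a ceiling. Any gap between the close of recruitment and session 1 adds to every entry.

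**4. Illustrative loss during the wait.** The documents give no withdrawal rate for this period, so the monthly rate r is an assumption, shown over a range. Loss for a block is 1 − (1 − r)^(wait in months), averaged over the stratified blocks and multiplied by 111.

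| Assumed r per month | Trial status dates | Table 2 |
|---|---|---|
| 1% | 2.8%, about 3 women | 0.2 |
| 2% | 5.6%, about 6 women | 0.4 |
| 3% | 8.2%, about 9 women | 0.6 |

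The average counts the last, part-filled pair of blocks as full. Weighting by women instead (nine pairs of 12, then 3 women with no wait) raises the top entry only from about 9 to about 10.

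**5. Reading the result.** Even the top entry is below the 22-woman allowance. The Sample size section does not say what period that allowance covers, so whether the loss is already provided for cannot be settled from the documents.

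**6. Order of baseline and allocation.** The phase list in Study design puts randomisation (phase 4) before baseline assessment (phase 5). The Requirement section puts the baseline interview directly after consent. If the phase list is followed, some baselines would also be taken after the arm is fixed.

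**The case against.** Sequential permuted blocks held by an independent third party are a standard and valid method, and no bias has been shown. Several further points stand.

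- **Disclosure.** A reader might infer that women know their arm for up to 7 months. The text does not say so. Sampling method says when the coordinator determines the group, and the blinding statement under Fig. 1 does not date disclosure. Arm-aware loss during the wait depends on women being told early, which is plausible but unstated. Loss after allocation is post-randomisation whenever they are told.
- **Timeline.** The long wait comes from dates described as anticipated and approximate. On Table 2 the problem almost disappears.
- **Size.** A reader might spread the 20% allowance over the 8 weeks plus 3 months (4.84 months) to get a hazard of −ln(0.8)/4.84 = 0.046 per month. Applied to waits uniform on 0 to 7 months, this gives 14.5% lost before session 1, about 21% by week 8 and about 32% by the 3-month visit. The documents do not support these figures. The allowance has no stated window, and nothing shows that a rate from the session period applies to a wait without sessions. The clock also starts at registration rather than when the block fills.
- **Retention and controls.** Data collection still seeks outcomes from women who stop sessions, so leaving the activity is not automatically missing data. The Follow-up section plans regular contact by local health staff. The Control group section gives controls counselling, educational sessions and a possible later invitation to similar activities, so it would be wrong to say that they get nothing.

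These points limit the size and certainty of the harm. None gives a reason to allocate early when everyone starts together.

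**Conclusion.** The gap between allocation and session 1 follows from the article's own text and is avoidable. On the Trial status dates it is about 6 to 7 months for the earliest blocks and about 3 months on average. On Table 2 it is days. These waits assume uniform registration and a start as soon as recruitment closes.

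The main risk is withdrawal or behaviour change that differs by arm before any session is held. A power shortfall is not shown. The 3 to 9 women rest on assumed rates of 1 to 3% per month, and the true number cannot be derived from the documents. The point is worth acting on because the remedy is cheap and works under either timeline, not because bias has been demonstrated.

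**What to change.** Reword Sampling method as follows.

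- Keep the blocks of six, the urban and rural strata, the registration order and the independent third party.
- Release all allocations in one step, after recruitment and baseline are complete and shortly before session 1.
- Define the intention-to-treat population from that date, and replace women who withdraw before it.

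Bring the phase list in Study design into line, so that baseline precedes randomisation. Reconcile the recruitment period in Table 2 with Trial status, and state when women are told their arm.

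**Cost.** The target of 111 does not change. Each replacement needs screening, consent and a face-to-face baseline interview. Women and staff get shorter notice of group assignment, which tightens the scheduling of sessions and transport.

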### Intervention

The interventions will consist of eight sessions, each lasting 120 min, held 3 days a week in an outdoor natural setting. Including 1 h of travel time, each session will last approximately 3 h. To facilitate participation, round-trip transportation will be arranged by the researcher using a bus service from local health centers to the session venue. Participants will gather at their assigned health center and will be returned there after each session. Each intervention session will be supervised by the researcher, accompanied by two trained health liaisons. These liaisons, local community health volunteers, will assist in ensuring participant safety, responding to concerns, and supporting effective engagement during each session. Participants will be advised to bring appropriate outdoor clothing, comfortable footwear, water, and any necessary medications. The researcher will use a session checklist to ensure all protocol components (e.g., warm-up, 50-min core activity, and discussion) are delivered. Participant attendance and engagement will be recorded.

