**Methods:**

This is a three-arm parallel randomized controlled trial (RCT) enrolling 111 women aged ≥ 60 from 9 urban and rural health centers in Khafr County, Iran. Participants will be randomized into the following: (1) Walking with meaningful conversation group, (2) meditation in nature group, and (3) control group with no intervention. Each intervention consists of eight 2-h sessions across 8 weeks. Assessments will occur at baseline, post-intervention (week 8), and 3-month follow-up using validated questionnaires on mental vitality and cognitive empowerment. The generalized estimating equation (GEE) model will be applied to analyze changes over time.

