### Study population and setting

The target population will consist of women aged 60 years and older residing in urban and rural areas of Khafr County, located in Fars Province, Iran, all of whom will be registered at urban and rural comprehensive health service centers. The inclusion criteria will be the absence of psychiatric disorders, cognitive impairment (Mini-Cog screened), balance disorders, and gait problems (tandem gait screened), willingness to participate in the study, and provision of informed consent. Individuals experiencing bereavement within the past 6 months and those missing at least one intervention session will be excluded from the study.

To maintain the integrity of the study results, participants should avoid enrolling in any formalized group activities with similar aims to the study interventions, such as scheduled walking clubs, guided meditation sessions, or therapeutic nature programs, for the duration of the 8-week intervention phase. There are no restrictions on standard medical care or informal daily routines.

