
**Table 1 Tab1:** Introducing thematic focus of verbal interaction in two intervention groups

Sessions	Intervention Group 1: Topics of meaningful conversation	Intervention Group 2: Topics of experience sharing
1	Intervention Group 1: Topics of meaningful conversation	Intervention Group 2: Topics of experience sharing
2	Sharing feelings and experiences from walking	Sharing experiences and feelings in meditation
3	Life experiences Participants can talk about positive and negative experiences in their life. This session helps them share their feelings and the lessons they have learned from life	Participants can talk about positive and negative experiences in their life. This session helps them share their feelings and the lessons they have learned from life and see how meditation helps them process these experiences
4	Exploring the impact of family and social relationships on quality of life. Participants can talk about their connections with family members, friends, and other community members and explore the challenges and joys of these relationships	Discussing psychological challenges and solutions
5	The impact of social activities A discussion of the importance of participating in social activities and how it impacts mental health and a sense of belonging	Analysis of advances and experiences in meditation
6	The importance of friendship Discussion on the role of friendships and social support in life. Participants can talk about close friends and the impact they have on their lives	Enhancing peace and continuing meditation practice
7	Challenges of aging Examine the challenges and problems that come with aging, including health problems, loneliness, and social changes, and self-care	Examine the impact of meditation on social interactions Examine how meditation can help improve social relationships, reduce stress in social encounters, and increase a sense of empathy and calm in relationships with others
8	Conclusion and the future A discussion about what they have learned from these sessions and a plan for the future. Participants can share their feelings and experiences about learning and positive changes	Final conclusion and exchange of views on experiences A discussion about what they have learned from these sessions and a plan for the future. Participants can share their feelings and experiences about learning and positive changes

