### Follow-up

To minimize intervention attrition rates and ensure participant retention, several strategies will be implemented:*Regular follow-up*: Weekly reminder phone calls or messages will be sent to participants to notify them of upcoming sessions and to emphasize the importance of their attendance. Local healthcare staff, health ambassadors, and liaisons will also maintain regular contact with participants to reinforce their sense of commitment to the study.*Supportive and motivational environment*: Participants will be continuously reminded of the significance of their participation and the potential benefits of the study on their well-being. A social and interactive atmosphere will be fostered during the sessions to promote a sense of belonging and motivation to remain engaged throughout the study.*Family and caregiver involvement*: Family members will be encouraged to support their older adult relatives by facilitating their attendance at sessions. Caregivers will be educated on their important role in promoting consistent participation and adherence to the study protocol. These strategies will help reduce attrition, enhance participant satisfaction and engagement, and ensure the collection of valid and reliable data.Furthermore, to facilitate attendance, round-trip transportation to the session venue will be provided. All participants will receive a summary of the aggregate study findings upon completion as tokens of appreciation.

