### Data collection

Data collection will be conducted in a structured and systematic manner to ensure the reliability and validity of the results. This process will begin with the acquisition of the necessary ethical and administrative approvals prior to any data collection activities. The study will also be registered with the Iranian Registry of Clinical Trials (IRCT20241023063481N1). To ensure data quality, all research personnel received standardized protocol training. The researcher will visit the selected health centers, explain the objectives and methodology of the study to the managers and healthcare staff, and obtain their consent to cooperate. Following this, the process of informing potential participants will begin. Assessments occur at three time points: baseline (pre-intervention), immediately post-intervention (week 8), and at a 3-month follow-up. At each stage, outcome measures (cognitive empowerment, mental vitality) are collected. To uphold the intention-to-treat principle, all participants initially randomized will be included in the final analysis. Individuals who choose to discontinue the active intervention sessions will still be invited to provide outcome data at the designated follow-up assessments (week 8 and 3 months), subject to their ongoing consent for this limited study involvement. Copies of all paper-based data collection forms are retained as study records and are available for review upon reasonable request.

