### Posttest (immediate follow-up)

Upon completion of the 8-week intervention period, a posttest will be administered to evaluate the immediate effects of the intervention on the participants. This assessment will include questionnaires on cognitive empowerment and mental vitality to identify any changes in the measured outcomes. The comparison will help determine the immediate impact of the intervention.

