### Outcomes

#### Primary outcome

The primary outcome is the change in Cognitive Empowerment score from baseline to the post-intervention assessment at week 8. To measure this variable, the Ability to Recognize Cognitive Changes questionnaire will be used. This questionnaire was designed and psychometrically evaluated by Tarighat et al. [14]. The questionnaire consisted of 25 questions that assessed older adults’ ability to recognize their own cognitive changes across 8 dimensions on a 3-point scale: physical strength (5 questions), self-esteem (5 questions), spirituality (2 questions), commitment (2 questions), role performance (4 questions), situation recognition (2 questions), self-management (3 questions), and self-assessment (2 questions). The total score ranged from 25 to 75. A score of 0 to 25 indicates that older adults’ ability to recognize cognitive changes is at an unfavorable level, 25 to 50 at a relatively favorable level, and a score above 50 at a favorable level. The questionnaire’s reliability and validity have been established, demonstrating satisfactory content and construct validity alongside a Cronbach’s alpha of 0.70.

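### Eight sessions held three days a week last under 3 weeks, which contradicts the 8-week intervention stated elsewhere

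*Protocol article*

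**What the plan says.** All references are to the protocol article.

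- **Intervention:** "The interventions will consist of eight sessions, each lasting 120 min, held 3 days a week in an outdoor natural setting". With travel, each session takes about 3 hours.
- **Abstract, Methods:** "Each intervention consists of eight 2-h sessions across 8 weeks".
- **Study population and setting:** the restriction on joining similar group activities applies "for the duration of the 8-week intervention phase".
- **Posttest (immediate follow-up):** "Upon completion of the 8-week intervention period, a posttest will be administered".
- **Data collection:** after baseline, the assessments are "immediately post-intervention (week 8), and at a 3-month follow-up".
- **Primary outcome:** "change in Cognitive Empowerment score from baseline to the post-intervention assessment at week 8".
- **Table 1:** topics are numbered 1 to 8, and session 8 is the closing one ("Conclusion and the future A discussion about what they have learned from these sessions and a plan for the future").
- **Follow-up (retention measures):** "Weekly reminder phone calls or messages will be sent to participants to notify them of upcoming sessions".
- **Table 2 (project plan):** one month is allotted to delivering the eight sessions.

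**The concern.** Session count, frequency and duration are tied together: any two fix the third. The article states all three, and they do not agree. Frequency and weekly dose are part of what defines the intervention, so a team working from the Intervention section and a team working from the abstract would deliver different programmes.

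Timing is also at stake. The article intends the primary assessment to come directly after the intervention and labels it week 8. Those are the same occasion only if the sessions run for 8 weeks. On a three-a-week schedule they separate, and three things move with them:

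- The primary outcome would be either an immediate effect or one measured weeks after the sessions ended.
- The 3-month follow-up, which is counted from the end of the intervention, would shift by the same gap.
- Most of the 8-week restriction on similar activities would fall after the last session.

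**Working it through.** **Inputs.** Eight sessions of 2 h (Intervention; abstract; count confirmed by Table 1). Three days a week and about 3 h per session with travel (Intervention). Duration of 8 weeks (abstract; Study population and setting; Posttest). Two active arms scheduled at different times, and three selected health centres (Sampling method).

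**Can the three figures hold together for one participant?**

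| Figures kept | Implied third figure | Conflicts with |
|---|---|---|
| 8 sessions, 8 weeks | 8/8 = 1 session a week | three days a week (Intervention) |
| 8 sessions, 3 a week | 8/3 = 2.67 weeks | 8 weeks (abstract and elsewhere) |
| 3 a week, 8 weeks | 3 × 8 = 24 sessions (48 h) | eight sessions (16 h) everywhere |

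**Weekly dose.** Once a week: 1 × 2 = 2 h of sessions, or 1 × 3 = 3 h with travel. Three times a week: 3 × 2 = 6 h, or 3 × 3 = 9 h. The ratio is 3. Total session time is 8 × 2 = 16 h on either schedule.

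**Could three days a week mean programme days rather than each woman's attendance?**

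- *Days divided between the two arms:* 2 × 8 = 16 arm-sessions. At three a week they last 16/3 = 5.3 weeks; spread over 8 weeks they need 16/8 = 2 days a week. Neither fits.
- *One day for each selected centre:* 3 centres × 1 day = 3 days a week, with each woman attending once a week for 8 weeks. This fits, but the article does not say it.

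**Gap to the primary assessment if three a week were followed.** Assume an alternate-day pattern, with sessions on days 0, 2, 4, 7, 9, 11, 14 and 16, and take week 8 as days 49 to 56.

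- Earliest: (49 − 16)/7 = 4.7 weeks after the last session.
- Latest: (56 − 16)/7 = 5.7 weeks.

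On a weekly schedule the last session is on day 49, so week 8 falls 0 to 1 week later, which fits an immediate post-test.

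**Table 2.** Its one month for eight sessions also differs from 8 weeks. That table is a rough workplan: it gives 2 weeks to the post-test and follow-up data together although follow-up is at 3 months, and it already lists the start of the interventions under an earlier stage. It is not counted here as a separate schedule.

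**The case against.** The strongest reply is that this is one stray phrase against a consistent schedule. The abstract gives both count and duration, two other sections give 8 weeks, and every statement that dates the primary assessment puts it at week 8. A reader of the whole article would settle on 8 weeks, and the gap of about 5 weeks arises only if staff follow the Intervention section and ignore the rest.

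The phrase may also describe programme days. Transport runs from the local health centres, women gather at their own assigned centre, and exactly three centres are selected, so one day per centre would reconcile everything. The weekly reminders fit that reading. Total dose is not in conflict, and nothing in the sample size or analysis changes.

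Much of this stands. Eight weeks is the likelier intention, the one-day-per-centre reading is possible, and the consequence for the primary assessment is conditional. It does not remove the point. The sentence describes how the sessions of the intervention are held, not how the venue is shared between centres, and nothing in the article supplies the missing link. Weekly reminders are compatible with one session a week but do not establish it. The sentence sits in the section that staff and replicators would use to deliver the programme, and on the benign reading it still needs the clause requested below.

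**Conclusion.** The concern holds and should be fixed. As written, the Intervention section gives about 2.7 weeks of sessions at 6 h a week, where the rest of the article describes 8 weeks at 2 h a week. If it were followed literally, the last session would precede week 8 by about 5 weeks (4.7 to 5.7, under the assumed alternate-day pattern and a week-8 window of days 49 to 56), and the primary assessment could not be both immediate and at week 8.

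The scope is limited. Session count, session length, total dose, sample size, analysis and the between-arm comparison are unaffected. What is at stake is correct delivery, replication and a single unambiguous date for the primary assessment.

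**What to change.** In the Intervention section, replace the three-days-a-week phrase with one session per week for each participant over 8 weeks. If the three days are programme days shared across centres or arms, say so and state that each woman attends once a week. Change the Table 2 entry for delivery of the interventions to 8 weeks for the eight sessions.

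If three sessions a week per participant is really intended, tie the primary assessment to the end of the last session (about week 3), on the same date in all three arms because controls have no sessions to anchor it. Then replace week 8 and the 8-week wording in the abstract, Study population and setting, Data collection, Posttest, Primary outcome, Secondary outcomes and Statistical methods.

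The first option costs one clause and one table cell, with no extra visits and no change to sample size or analysis. The Trial status section says recruitment had not started at this protocol version, so on that footing the wording could be corrected before delivery.
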